#### Serological survey—laboratory testing

From the samples collected in the serosurvey, about 200 µL of serum were used and tested at a local laboratory using dengue IgG ELISA (Panbio Dengue IgG Indirect ELISA, Alere North America, Florida, USA). After ELISA testing for dengue IgG at the local laboratories, samples were shipped to IVI. Given potential serological cross-reactivity among flaviviruses,^39^ flow cytometry-based neutralisation assays will be performed against selected flaviviruses to include yellow fever virus, West Nile virus, Zika virus and Japanese Encephalitis virus, in addition to DENV 1-4, at the Clinical Immunology Lab of IVI.^40 41^ About 50 samples per bleed for four bleeds in Burkina Faso and two bleeds in Gabon and Kenya will be tested.

About 1000 µL of serum is allotted for this procedure. The flow cytometry-based neutralisation assays are performed in duplicate in 96-well cell culture plates with flat-bottom wells, each containing DC-SIGN-expressing U937 cells.^40^ The amount of virus used in the assay infects between 7% and 15% of the cells. Human immune sera are serially diluted and the virus is preincubated with the sera for 1 hour at 37°C.^40^ The cells are washed, the virus and serum mixture is added to the cells for 1 hour at 37°C and the cells are further incubated for 24–48 hours at 37°C in 5% CO_2_. The cells are fixed, permeabilised and stained with fluoresce-conjugated monoclonal antibody 4G2, which recognises the flavivirus E protein.^42^ FACScan flow cytometer (Becton Dickinson, San Diego, California, USA) is used to analyse the cells.^40^ The serum dilution that neutralises 50% of the viruses is calculated by nonlinear, dose-response regression analysis with Prism 4.0 software (GraphPad Software, San Diego, California, USA).

In addition, a Luminex-based multiplex immunoassay will be performed on a randomly selected subsample to assess for IgG to different flaviviruses.^43^ About 200 samples per bleed for four bleeds in Burkina Faso and two bleeds in Gabon will be tested. Detection of IgG against ZIKV and each of the four DENV serotypes will be performed on patient serum samples using an in-house microsphere-based multiplex immunoassay (arbo-MIA) at the Clinical Immunology Lab of IVI.^44 45^ The arbo-MIA is based on a mixture of microspheres covalently coupled with either DENV-1, DENV-2, DENV-3, DENV-4 or ZIKV recombinant antigens (E protein domain III) produced in Drosophila S2 expression system. Briefly, microsphere mixtures were sequentially incubated in the dark under constant shaking with a 1:400 dilution of patient serum samples, with 2 µg/mL antihuman IgG biotin-conjugated antibody (Jackson Immunoresearch, West Grove, Pennsylvania, USA) and with 2 µg/mL streptavidin-R-phycoerythrin conjugate (Life technologies). After the final incubation, the median fluorescence intensity (MFI) of each microsphere set is quantified using a BioPlex 200 instrument (Bio-Rad Laboratories, Hercules, California, USA). Samples are considered seropositive if the ratio of MFI values obtained for the viral antigen to the control antigen is superior to the defined cut-off. The cut-off of the MIA is determined for each viral antigen by receiving operating characteristic (ROC) curve analysis using well-characterised sera.

In Lambaréné, the enrolment bleed took place in November–December 2015, while the second blood collection occurred in May 2016. In Ouagadougou, the enrolment bleed took place in May–June 2015 with follow-up blood collections in December 2015, June 2016 and January 2017. In Mombasa, the enrolment bleed took place in May 2016 with the second blood collection in November 2016–February 2017.

#### Healthcare utilisation survey

As the passive fever surveillance was conducted at study facilities, patients with potential dengue could be missed if they seek care elsewhere. To identify the proportion of fever and dengue cases potentially missed by the passive surveillance system due to patients living in the study area but seeking care outside of study facilities, a population-based healthcare utilisation survey was conducted in 400 randomly selected households from the study catchment area to characterise the healthcare utilisation patterns of the households when they have (self-reported) febrile episodes among the family members. In addition to assessing health-seeking behaviours of the residents, preferences in terms of health-seeking behaviour and respective reasons for their preferences were investigated. The questionnaire was administered to 400 heads of households. Among 3000 residents who participated in the serosurvey, there were about 600 households. From these households, 400 heads of households were randomly selected and offered enrolment in the health utilisation survey. Heads of households or a senior representative within the household were asked questions on health seeking patterns of their family members.

### Study questionnaires

For the fever surveillance study, questionnaires were administered at the acute illness visit and the convalescent visit. The convalescent visit may take place at the healthcare facility (10–14 days later) or at the patient’s home (15–21 days after the acute visit), according to patient preference and availability. The questionnaires were completed by medical staff of the study facilities, including demographic and clinical information (eg, signs, symptoms, past medical history, treatments prescribed and diagnoses). The same staff also completed the follow-up questionnaire at the convalescent visit within 21 days from the acute visit. Study nurses completed surveillance enrolment log. Lab technicians completed the lab section (mostly dengue-related diagnostics) and the forms were compiled by the study coordinator on site.

For the serosurvey component, questionnaires were administered at the household by trained field team staff at each serosurvey visit. Study nurses completed the questionnaire after a brief physical and medical examination. At the follow-up visit(s) in about 6 months, the same staff made the household visits to complete the follow-up questionnaire. Enrolment log was maintained by the study coordinator on site.

### Variables of the surveillance questionnaires

The variables collected are listed in table 1.

**Table 1 T1:** List of variables collected in the passive fever surveillance data collection form

Topic	Description	Items
Basic information	Demographic and basic information about the patient and the treatment received	Type of treatment, where patient is enrolled (IPD vs OPD) Date of fever onset, duration of fever Current temperature Tourniquet test results Patient’s address (district and village-level) Date of visit, date of birth, age and sex Weight and height
General health condition	Current condition of the patient (self-report) and underlying diseases of the patient	How well the patient could handle daily activities Pre-existing conditions
Signs and symptoms during this illness	A set of signs and symptoms that may be related to fever and dengue (dengue fever and dengue haemorrhagic fever) at both visits 1 and 2	Rash, fatigue, headache, retro-orbital pain, neck/ear pain, sore throat, breathing difficulty, cough, expectoration, gastrointestinal signs (nausea/vomiting, diarrhoea, abdominal pain and so on), haemorrhagic signs (nose/gum bleeding, ecchymosis, petechiae and so on), signs of shock (cyanosis, capillary refill), arthralgia, myalgia, loss of appetite, jaundice and so on
Medical history	Previous dengue-related or other flavivirus infection as well as vaccination history (self-report)	Previous dengue infection and related hospitalisation Previous infection to other commonly circulating arboviral infection in the area (ie, Yellow fever vaccination history)
Laboratory findings	Records from the routine laboratory tests widely used in clinical fever/dengue patient management, as part of the hospital care procedure	Platelet count, haematocrit, haemoglobin, leucocytes, neutrophils, protein level, AST, ALT, urine test results and so on
Clinical diagnosis	Clinician’s diagnosis with or without referring to the RDT	Diagnosis given by the physician based on clinical presentation after physical examination of the patient
Dengue testing results	Results from the dengue tests, mainly RDTs for dengue as well as other commonly circulating arbovirus in the area	Dates of blood draw Test results of the RDT IgM/IgG capture ELISA results PCR results (if available)
Treatment	Medicine(s) prescribed and the starting and end dates	Antibiotics, paracetamol, ibuprofen, aspirin and others that may be site-specifically prescribed
Outcome	Outcome of this particular visit	Hospitalised, returned home or referral
Hospitalisation	Information collected only among hospitalised patients in the surveillance to record other severe signs and progression of illness	Admission and discharge diagnoses Presence of haemorrhagic signs or shock syndrome
Hospital charges	Expenses and hospital charges incurred by patient on the visit 1	Amount of the out of pocket payment by the patient or the family/or guardian Breakdown of the hospital charges (laboratory, medication, admission-related charges)
Final outcome	Outcome of the patient’s illness at the second visit	Final diagnosis given for the patient, outcome of illness Completion of study participation (early termination and the reason and so on)

ALT, Alanine AminoTransferase; AST, Aspartate aminotransferase; IPD, Inpatient department; OPD, Outpatient department; RDT, Rapid Diagnostic Test.

### Planned statistical analysis

From the fever surveillance data, incidence of symptomatic dengue among patients that seek healthcare at the study facilities will be calculated. Age-specific incidence rates in all the children and adults will be determined by referring to the size and distribution of the general population of the study area at the time of surveillance as the denominator in calculation of the incidence of symptomatic dengue cases. Each person residing in the study area is assumed to contribute 12 months of person time to the denominator. Although the study areas all report a low migration rate, the in-migration is assumed to balance the out-migration of the population during the study period. Age-specific incidence of symptomatic dengue will be calculated by using age-specific denominators and the number of symptomatic dengue cases in eligible individuals as the numerator.

Using the data collected in the Healthcare Utilisation Survey, the proportion of febrile cases missed by the passive surveillance system will be determined. Then using the proportion, the numerator will be further adjusted in recognition of those missed fever cases from the study area, which could have been dengue. Also, comparison will be made between those that agreed to participate and those that declined participation among the eligible potential enrolees. The enrolment log, which records basic information obtained during the screening process of potential enrolees, will be reviewed. In addition to checking that our sample of febrile cases is representative of febrile patients of the general population in the catchment area, refusal rates will be determined based on information in the log. Then, the refusal rates will be used to adjust the numerator.

SPSS software will be used for analysis of the fever surveillance data. Multivariable logistic regression will be used to compare confirmed patients with dengue versus patients with non-dengue febrile in terms of symptomatic presentation, based on signs and symptoms collected from all patients with laboratory-confirmed dengue by serology and RT-PCR, adjusting for possible confounders, such as age, days since onset of fever, primary versus secondary infection, inpatient versus outpatient and so on. Differences in symptomatic complex of dengue fever (DF) (and DHF, if data allows) by age and serotype will be also determined using multivariable logistic regression.

As outpatient disease accounts for the greater part of dengue disease burden, clinical profile of individuals with DENV infection will be characterised by the type of treatment (hospitalised vs outpatients) as well as by severity of the disease (severe vs non-severe by the 2009 WHO criteria).^46^ Classification is determined after the course of illness is completed (typically during the convalescent visit). Symptomatic dengue is classified as outpatient or hospitalised. Progression of dengue is recorded as DF, DHF I, DHF II, DHF III or DHF IV, and clinical patterns will be compared by the severity grade.^46 47^ These will be compared with results obtained from other DVI studies in Latin America (Colombia) and Asia (Thailand, Vietnam and Cambodia). Overall, comparisons will be made across Burkina Faso, Gabon and Kenya.

With the age-stratified sera that reflect the age distribution of the general population of the country, the serological survey sampling strategy ensures sufficient subjects to obtain precise age-specific estimates of seropositivity and seroconversion of the catchment area population. The seroconversion rate and change in the immune status will be determined by age group during the study period. The age-stratified serosurvey data will also allow calculation of the force of infection of dengue in the study population. After enrolment, there are subjects who drop out in the follow-up bleeds about 6 months later. Basic demographic information will be compared between those that completed participation and those with incomplete participation to check whether study subjects represent the catchment area population. Comparisons will be made among Burkina Faso, Gabon and Kenya.

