### Study participants

For the passive facility-based fever surveillance, individuals who met the following criteria were eligible for study enrolment:Age 1–55 years old.Resident of the catchment area covered by healthcare facilities participating in the study, without plans to move out of the catchment area within 12 months.Signed informed consent and assent for those aged between 7 (13 for Kenya) and 17 years.Patients presenting with current fever (axillary temperature ≥37.5°C) or history of fever for ≤7 days duration without localising signs (fever caused by a localised infection as well as fever with a known and confirmed aetiology other than dengue, such as malaria confirmed by malaria RDT, as listed in the patient identification standard operating procedure [SOP]).

For the serological survey, criteria 1–3 were applied. For the healthcare utilisation survey, household interviews were conducted among the heads or representatives of the household invited from each family participating in the serosurvey.

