### Study area and population

Burkina Faso, located in West Africa, has a population of 14 017 462. The country is mainly rural with about 29% of the population reported to be living in urban areas in 2014. However, Burkina Faso is urbanising rapidly and is positioned as the country with the fourth fastest urbanisation in the last 25 years.^27 28^ The capital, Ouagadougou, has a population of 2 741 128. The majority of the population live in urban settings. About 45% of the population are under 15 years of age.^29^ The city is divided into 12 districts and 52 sectors. Ouagadougou is the country’s largest city and the cultural and economic centre. The city is part of the Soudano-Sahelian area, with a rainfall of about 800 mm per year. The rainy season is from May to October, with a mean temperature of 28°C (82°F). The cold season runs from December to January, with a minimum average temperature of 16°C (61°F). During the hot season, which runs from March to May, the temperature can reach as high as 43°C (109°F).

The HDSS is in place in Ouagadougou. Ouaga-HDSS monitors a population of 81 717 residents; according to this surveillance system, the city population is very stable with a rate of migration of 4.1% and more than 80% of the inhabitants with ownership of their houses [20]. A map of the city and the study area is shown in figure 2.

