### Study components

#### Fever surveillance—design and methods

To determine burden due to symptomatic dengue in each of the three sites in Burkina Faso, Gabon and Kenya, passive facility-based fever surveillance was implemented in a well-defined catchment area population. In Burkina Faso, the surveillance study was initiated in December 2014 in five selected primary healthcare centres, locally called ‘Centre de Santé et de Promotion Sociale’, in the municipality of Ouagadougou, with a catchment population of 105 000 residents. This project was implemented in collaboration with Centre Muraz in Bobo-Dioulasso, EQUITE sante programme (a collaborative programme between University of Montreal and Action-Gouvernance-Integration-Reinforcement, AGIR, based in Ouagadougou, funded by the Canadian Institute of Health Research) and DVI. In Gabon, the surveillance study was initiated in the ASH serving a catchment population of 130 000 residents in the Moyen-Ogooué and surroundings within Lambaréné, in collaboration with CERMEL and Institute of Tropical Medicine in Tubingen, Germany. In Kenya, the surveillance study was implemented at Ganjoni dispensary, Tudor subcounty Hospital and Coast Provincial General Hospital, serving a catchment population of 70 000 residents in Mombasa, in collaboration with Kenya Medical Research Institute and Ministry of Health of Kenya.

As described in figure 5, both outpatients and inpatients at the designated study facilities, who meet inclusion criteria as mentioned earlier were tested for dengue, first with SD Dengue Duo RDT. Dengue confirmation was done by detection of dengue virus in serum samples using PCR as well as antidengue IgM and IgG antibodies in acute and convalescent serum by ELISA (SD Dengue IgM & IgG capture ELISA tests, Standard Diagnostics, Yongin-Si, Korea).^10 37^ Every consecutive patient meeting inclusion criteria was eligible for enrolment during the study period. Infants<1 year old were not included due to operational limitations, such as difficulty of infantile bleeding.

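### Cases are counted only among eligible residents (aged 1–55, not planning to move), but the incidence denominator is every resident, and no planned adjustment closes the gap

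*Protocol article*

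**What the plan says.** The Planned statistical analysis section of the protocol article describes the denominator as obtained "by referring to the size and distribution of the general population of the study area at the time of surveillance as the denominator". It adds: "Each person residing in the study area is assumed to contribute 12 months of person time to the denominator". It promises age-specific rates for children and adults without an age limit. The last sentence of the same paragraph says that age-specific incidence will use age-specific denominators, with "the number of symptomatic dengue cases in eligible individuals as the numerator".

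Who is eligible is set under Study participants: "Age 1–55 years old", and resident in the catchment area "without plans to move out of the catchment area within 12 months". The section on fever surveillance design confirms the lower limit: "Infants<1 year old were not included due to operational limitations".

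Three provisions bear on people the surveillance misses. The numerator is scaled up for fevers treated outside the study facilities, using the healthcare utilisation survey. It is also adjusted for refusals among eligible people who were screened. The Discussion says that inverse probability weighting will carry these same two adjustments. In addition, inward and outward migration are assumed to balance.

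**The concern.** An incidence rate is interpretable only if everyone who contributes person-time could have been counted as a case. Here three groups contribute person-time but can never enter the numerator: infants, people over 55, and residents who plan to move within 12 months. Wherever they remain in the denominator, the rate is biased downward.

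The error is systematic, so a larger sample does not reduce it. It also concerns a main output of the study: incidence that is meant to be comparable across three sites and with studies by the same initiative elsewhere.

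The residence rule deserves particular attention. Fever-surveillance participants are followed only briefly (staff "completed the follow-up questionnaire at the convalescent visit within 21 days from the acute visit"), so follow-up there does not by itself call for a 12-month residence horizon. The serosurvey uses the same criterion and has repeat bleeds about six months apart. Whatever the reason for the rule, its effect on fever surveillance is to remove cases while leaving the people in the denominator.

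**Working it through.** The article gives no dilution factor and no population share under 1 or over 55, so there is no stated figure to reproduce. The size can only be bounded.

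**Inputs**
- Age limits 1–55 and the residence rule: Study participants.
- Migration rate: Study area and population, for Ouagadougou only: "the city population is very stable with a rate of migration of 4.1" per cent. It measures migration, not stated intention to move, so it is only a proxy.
- Share of residents outside 1–55: not in the article. Assumed 5.5–12% (infants 2.5–4%, over 55 3–8%).

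**Formula**

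Let *a* be the share of the denominator outside ages 1–55 and *m* the share planning to move, taken as independent of age. Then

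reported / true = (1 − *a*)(1 − *m*).

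Read as the ratio to the rate in eligible residents, this is direct arithmetic. Read as the ratio to the rate in all residents, it also assumes that the ineligible have the same risk as the eligible.

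**Results**

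| Rate | *a* | *m* | Reported / true |
|---|---|---|---|
| Band wholly inside 1–55, age term only | 0 | 0 | 1.000 |
| Band wholly inside 1–55, movers at the proxy | 0 | 0.041 | 0.959 |
| Band wholly inside 1–55, movers assumed 10% | 0 | 0.10 | 0.900 |
| Pooled over all residents, age term only, low | 0.055 | 0 | 0.945 |
| Pooled over all residents, age term only, high | 0.12 | 0 | 0.880 |
| Pooled, low age share plus proxy movers | 0.055 | 0.041 | 0.945 × 0.959 = 0.906 |
| Pooled, high age share plus proxy movers | 0.12 | 0.041 | 0.880 × 0.959 = 0.844 |

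The mover term alone implies a correction factor of 1/0.959 = 1.043. As an illustration of an edge band, a 0–4 group in which infants are assumed to be one fifth of the person-time gives 0.80 from the age term. The article does not propose such a band.

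**Do the planned adjustments cover these groups?**
- Care sought elsewhere: corrects for fevers that did not reach a study facility, not for people who attended and were ineligible.
- Refusals: calculated among eligible people, so excluded movers are not in that count.
- Inverse probability weighting: built from those same two proportions.
- Balanced migration: keeps the population size constant and says nothing about who could be counted as a case.
- Review of the enrolment log for representativeness: a check, with no correction attached.

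None of them restores the excluded groups.

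**The case against.** The strongest reply is that the paragraph itself calls for age-specific denominators, and that the general population can be read simply as the source of those age counts. On that reading infants and people over 55 add nothing to any band inside 1–55. This stands, and it removes the age problem for such bands. It is also true that the article defines no pooled all-age rate and no 0–4 or open-ended top band, and that the age groups it gives for the serosurvey (1–14 and 15–55) match eligibility. Choosing exact bands may properly be left to a fuller document. What remains is that the current wording never limits the denominator to 1–55 and promises rates for children and adults without limit.

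A second reply is that the mover effect is small: about 4% on a weak proxy, in a city described as stable, against a planned margin of error of 25% of the true incidence. The smallness is fair. But a one-sided bias is not part of sampling error, and the age-specific denominators do nothing about movers.

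A reader might infer three stronger claims that the document does not support:
- That all the incidence rates are understated by 9–16%. That range (ratios 0.906 to 0.844) applies only to a pooled rate over all residents, under assumed age shares combined with the mover proxy.
- That the between-site comparison is distorted. The mismatch could differ by site, but no mobility figure is given for Lambaréné or Mombasa.
- That the residence criterion should be dropped from fever surveillance. Surveillance had ended at all sites by May 2017, so this is not available, and the article does not state the rule's rationale.

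**Conclusion.** The mismatch between numerator and denominator is real, and its direction is downward. Its size depends on the rate reported:

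- **Bands wholly inside 1–55:** no age dilution. Only the mover term remains, about 4% in Ouagadougou if the migration rate approximates the share planning to move, and unknown at the other two sites.
- **A pooled rate over all residents:** a further 5.5–12% from age, if that share of residents falls outside 1–55. This share is an assumption.
- **Edge bands that include infants or people over 55:** biased downward by the ineligible share of the band. Whether such bands will be used is not stated.

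The effect is modest, but it is systematic, touches a main estimate, is not listed among the limitations, and can be removed or bounded at the analysis stage.

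**What to change.** 1. State that the incidence denominator is residents aged 1–55, with the first band starting at age 1 and the last ending at 55. Calculate any pooled rate on the same population.
2. Replace the promise of rates for all children and adults by rates for residents aged 1–55.
3. Where the enrolment log records a planned move as the reason for exclusion, include those febrile residents with the refusals in the non-enrolment weight. Where it does not, report incidence over a stated range of mover shares (for example 0%, 4.1% and 10%) at each site.

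The cost is a change of wording, age counts that the age-specific rates already require, a little more analysis, and a slightly smaller stated population at risk. The article says only that the log holds basic screening information, so item 3 may have to rest on the sensitivity range.

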**Ethics and dissemination:**

By standardising methods to evaluate dengue burden across several sites in Africa, these studies will generate evidence for dengue burden in Africa and data will be disseminated as publication in peer-review journals in 2018.

Strengths and limitations of this studyThere have not been population-based studies conducted with a multidisciplinary approach (ie, surveillance, healthcare utilisation and serosurvey in one catchment area population). Data from the passive surveillance will be used to calculate annual incidences of dengue and data from the serosurvey will estimate the force of infection and prevalence.The studies were conducted in three locations in Africa, based on standardised methods and laboratory algorithm. Thus, comparison by site would be possible.This is not a cohort study. The passive facility-based surveillance may lead to underestimation of the burden of dengue fever by measuring incidence based on only those that sought care at our study facilities.There may be limited generalisability of our study results to other dengue-endemic parts of Africa.

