**Figure 5 F5:**
[figure not shown]
Patient flow in the fever surveillance. Eligible febrile patients identified and enrolled as study subjects followed these steps to complete participation in the passive fever surveillance. * A small number of those samples that are negative on ELISA or NS1 are tested with PCR to exclude false negative results of the ELISA. CRF, case report form.

In Ouagadougou, Burkina Faso, the fever surveillance was initiated in December 2014 and continued until February 2017 (approximately 2 years). In Lambaréné, Gabon, the fever surveillance was initiated in April 2015 and continued until January 2017 (approximately 1.5 years). In Mombasa, Kenya, the fever surveillance was initiated in March 2016 and continued until May 2017 (15 months).

Among subjects enrolled in the fever surveillance, those who were positive by dengue rapid diagnostic test were offered further enrolment in the cost-of-illness survey, consisting of interviews on the day of acute illness visit, day 10–14 from the first visit and day 28, if illness continues. The cost-of-illness survey questionnaire was designed to estimate the direct medical, direct non-medical and indirect costs associated with dengue-positive patients identified at study facilities. This survey also estimates the cost of treating dengue at the facility level. Data were gathered by linking patients’ medical records concerning outpatient visits, inpatient visits and service consumption (eg, diagnostic tests, medication and other services provided to patients). The cost-of-illness portion of the study will be described separately.

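### The incidence denominator is fixed at 12 months per resident, but no matching 12-month case window is stated although surveillance ran about 14 to 27 months depending on site

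*Protocol article*

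**What the plan says.** The section Planned statistical analysis in the protocol article sets the denominator: "Each person residing in the study area is assumed to contribute 12 months of person time to the denominator". It supports this with a stable-population assumption, namely that "the in-migration is assumed to balance the out-migration of the population during the study period". Age-specific incidence is then to be obtained "using age-specific denominators and the number of symptomatic dengue cases in eligible individuals as the numerator". No case window and no division by years of surveillance is given there.

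The section on fever surveillance design and methods says of recruitment: "Every consecutive patient meeting inclusion criteria was eligible for enrolment during the study period". The text after the Figure 5 caption dates the surveillance at each site:

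- Ouagadougou: "the fever surveillance was initiated in December 2014 and continued until February 2017 (approximately 2 years".
- Lambaréné: "the fever surveillance was initiated in April 2015 and continued until January 2017 (approximately 1.5 years".
- Mombasa: "the fever surveillance was initiated in March 2016 and continued until May 2017 (15 months".

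The strengths and limitations box after the abstract names the target measure: "Data from the passive surveillance will be used to calculate annual incidences of dengue". Planned statistical analysis also announces comparisons across the three countries.

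**The concern.** A rate needs cases and person-time from the same period. Here the person-time is one year per resident at every site, while the only period described for finding cases is the whole surveillance period. That period is longer than a year everywhere and differs between sites. Taken literally, the rule divides more than a year of cases by one year of person-time, and the mismatch is largest in Ouagadougou and smallest in Mombasa.

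Age-specific incidence is the main output of the surveillance, and comparable incidence across sites is a stated purpose of the standardised design. The Discussion expects the burden data to inform judgements on dengue vaccination. An error that depends on how long each site stayed open would affect the level of each rate and the contrasts between sites.

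**Working it through.** **Inputs.** Person-time per resident is 12 months (Planned statistical analysis). Start and end months come from the text after the Figure 5 caption. The population is stable over the study period (Planned statistical analysis).

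**Step 1: length of surveillance.** Only months are given, so the count depends on convention. The month difference and the inclusive month count are:

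| Site | Dates | Month difference | Inclusive count | Article's label |
|---|---|---|---|---|
| Ouagadougou | Dec 2014 – Feb 2017 | 26 | 27 | about 2 years (24) |
| Lambaréné | Apr 2015 – Jan 2017 | 21 | 22 | about 1.5 years (18) |
| Mombasa | Mar 2016 – May 2017 | 14 | 15 | 15 months |

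The Mombasa label is reproduced by the inclusive count. The other two labels are rounded and fall short of the dates. If surveillance began at the end of the first month and stopped at the start of the last, the minimum is about 25.1 months for Ouagadougou and 20.1 for Lambaréné. Hence the ranges of about 25–27, 20–22 and 14–15 months.

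**Step 2: overstatement if all accrued cases are counted.** With a stable population N and m months of surveillance, the matching person-time is N × m/12 years. The stated rule gives N × 1 year. N cancels, so the overstatement is m/12:

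- Ouagadougou: 25.1/12 = 2.09 to 27/12 = 2.25; on the label, 24/12 = 2.0.
- Lambaréné: 20.1/12 = 1.68 to 22/12 = 1.83; on the label, 18/12 = 1.5.
- Mombasa: 14/12 = 1.17 to 15/12 = 1.25; on the label, 15/12 = 1.25.

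As an illustration, assume a true rate of 2.0 per 1000 person-years at every site and take the inclusive counts. The 12-month denominator returns 2.0 × 2.25 = 4.50 in Ouagadougou, 2.0 × 1.83 = 3.67 in Lambaréné and 2.0 × 1.25 = 2.50 in Mombasa. Person-time of m/12 years per resident returns 2.0 at all three.

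**Step 3: spurious site ratios at equal true incidence.**

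- Burkina Faso to Kenya: 24/15 = 1.60 (labels), 27/15 = 1.80 (inclusive), 26/14 = 1.86 (difference).
- Gabon to Kenya: 18/15 = 1.20, 22/15 = 1.47, 21/14 = 1.50.
- Burkina Faso to Gabon: 24/18 = 1.33, 27/22 = 1.23, 26/21 = 1.24.

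**Step 4: does another planned step remove it?** The corrections for care sought elsewhere and for refusal rescale by the share of fevers missed. They leave the length of observation unchanged, so the factor m/12 carries through.

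**Step 5: the alternative reading.** If each rate uses the cases of one 12-month block over 12 months of person-time per resident, the factor is 12/12 = 1 and nothing is inflated.

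**The case against.** The strongest reply is that the article promises annual incidences, in the plural. For an annual incidence in a stable population, one person-year per resident is the standard denominator, and balanced migration is its usual justification. Every site ran for at least 12 months, so each can supply at least one complete block. The sentence on consecutive patients is an enrolment rule and does not define the numerator. A condensed article may also leave the dates of annual blocks to the full protocol.

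Much of this stands. A reader might infer that the rates will be up to 2.25 times too high and the ranking of sites wrong. The document does not support that as a fact. It shows no computed rate, and the annual reading would remove the inflation entirely. Even if all cases were pooled, the order of two sites could change only where their true rates differ by less than the spurious ratio.

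What does not stand is that the annual reading is what the text says. The denominator rule is explicit, the numerator has no window, and the neighbouring sentence on migration refers to the whole study period. Nor are the periods whole years. Crediting 12 months for each started year would give 36, 24 and 24 months of person-time against 26–27, 21–22 and 14–15 observed. Rates would then be understated by about 25–28%, 8–13% and 38–42%. The annual reading works only with complete blocks, and none are stated.

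**Conclusion.** The point holds as a mismatch between a fixed 12-month denominator and an unrestricted numerator. Followed as written, with all cases from the full surveillance period counted and a stable population, the rule overstates incidence by about 2.1–2.25 times in Burkina Faso, 1.7–1.8 in Gabon and 1.2–1.25 in Kenya. The article's rounded durations give 2.0, 1.5 and 1.25. At equal true incidence Burkina Faso would appear about 1.6–1.9 times Kenya. If cases are counted in complete 12-month blocks, the overstatement is nil. The text does not settle which applies, so the size is conditional, but the need to settle it is not: the choice governs the main surveillance estimate and the comparison across sites.

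Gabon's rounded duration is a side issue. It matters only if 18 months were used as person-time, when rates would still be about 12–22% too high (20.1/18 = 1.12; 22/18 = 1.22).

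**What to change.** Replace the 12-month sentence in Planned statistical analysis with one of two rules, and use the same rule at all sites and for the between-site comparison:

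1. Person-years = age-specific population × actual surveillance months at that site / 12, with all cases from those months in the numerator.
2. Keep 12 months per resident, and restrict the numerator to complete 12-month blocks whose start and end dates are stated for each site. The dates allow two blocks in Ouagadougou and one each in Lambaréné and Mombasa.

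Reconcile Gabon's stated duration with its dates if it is to enter the person-time.

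Either rule takes a sentence and no new data. The first uses every case but gives extra weight to calendar months covered more often; Mombasa's 15 months, for example, include March to May twice. The second avoids that but leaves out the cases of about 2–3 months in Ouagadougou, 9–10 in Lambaréné and 2–3 in Mombasa. If the analysts already count by annual block, stating the blocks is all that is needed and no rate changes.
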